**Discussion:**

We believed that the rate of postoperative complication of LE will be comparable to that of TME in mid-to-low advanced rectal cancer patients with a favorable response after pre-CRT.

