#### Primary outcome

The primary endpoint of the current study is the rate of postoperative complications. Postoperative events occurring up to 30 days after surgery will be evaluated by the Clavien-Dindo Classification, any events grade 2 or higher will be considered postoperative complications.

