#### Sample size calculation

The sample size was calculated based on two-sided non-inferiority test with for 80% power and a significant level of 0.05, one-sided. We assume that the rate of postoperative complications on day 30 will be 15% in the TME group and 15% in the LE group, with a non-inferiority margin of 15%. Based on these calculations, a total of 67 patients should be allocated to each group; assuming a 5% dropout rate, we plan to enroll 140 patients. The 15% rate of postoperative complications cited above is based on published findings [26–28, 30].

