### Data analysis

The intent-to-treat (ITT) analysis set will include all subjects who are randomized into a surgery group. The modified ITT analysis set will include all subjects who undergo pre-CRT. The per protocol (PP) analysis set will include only the subjects in the ITT group who complete the study protocol. Patients who withdraw informed consent or who develop serious adverse events will be excluded from the PP analysis set. The modified ITT set will be used for analysis of primary and secondary study endpoints. The PP analysis set will be used for subgroup analysis. Baseline characteristics will also be analyzed in the ITT group.

Variables and outcomes will be analyzed using chi-square tests (for proportions) or Fischer’s exact test, as appropriate. Continuous data will be analyzed using Student’s t-test or Mann-Whitney U tests, as appropriate. Cumulative risk rates will be calculated using the Kaplan-Meier method and compared using log-rank tests. Multivariate analyses using binary logistic regression will be used to assess the risk of postoperative complications. Statistical significance will be defined as *p* < 0.05, and all analyses will be performed using SPSS software, version 22 (IBM Corporation, Armonk, NY, USA).

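### The trial is sized for non-inferiority with a 15-point margin, but the article's analysis section gives proportions only tests of equality and never uses the margin

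*Protocol article*

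**What the plan says.** The primary endpoint is binary. Under Primary outcome, events up to 30 days after surgery are graded by Clavien-Dindo, and "any events grade 2 or higher will be considered postoperative complications".

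Sample size calculation sets a non-inferiority hypothesis: "The sample size was calculated based on two-sided non-inferiority test with for 80% power and a significant level of 0.05, one-sided". It assumes that "the rate of postoperative complications on day 30 will be 15% in the TME group and 15% in the LE group". The same sentence fixes how much worse LE may be, in the words "with a non-inferiority margin of 15" per cent. From this, "a total of 67 patients should be allocated to each group", and, "assuming a 5% dropout rate, we plan to enroll 140 patients".

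Data analysis then states how results will be tested: "Variables and outcomes will be analyzed using chi-square tests (for proportions"), or Fisher's exact test where appropriate. Continuous data get t or Mann-Whitney tests, time-to-event data get Kaplan-Meier curves and log-rank tests, and complication risk gets binary logistic regression. One threshold, p < 0.05, covers everything. The section gives no confidence interval for the difference, no margin and no one-sided level. The margin appears nowhere outside Sample size calculation.

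The Discussion paragraph of the Abstract gives the authors' expectation that "the rate of postoperative complication of LE will be comparable to that of TME".

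**The concern.** A non-inferiority trial has to reject the null hypothesis that LE is worse than TME by 15 points or more. Chi-square and Fisher's exact tests have a different null, that the two rates are equal. Rejecting equality in the direction of more complications with LE does not support non-inferiority. Failing to reject equality does not exclude a 15-point excess. So the hypothesis that fixed the sample size and the test named for proportions answer different questions.

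The primary conclusion is at stake. The 80% power was computed for a comparison with the margin, and Data analysis names no such comparison. If the section were followed literally, the only result that could look like support for comparable rates, short of LE being significantly better, is a non-significant p-value. The chance of obtaining that when LE is truly 15 points worse is not held at 5%.

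The article's own Discussion makes the unfavourable direction more than theoretical. It cites a prospective study in which the overall complication rate of LE after chemoradiotherapy is described as higher than that of TME.

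**Working it through.** **Inputs** (Sample size calculation): both rates 0.15, margin 0.15, one-sided alpha 0.05, power 0.80, 67 per arm. I take the margin as absolute, because the text gives only a percentage. A relative margin would be 0.15 × 0.15 = 0.0225 and would need 0.255 × 6.183 / 0.0225² ≈ 3,100 per arm, which plainly was not intended.

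**1. The plan's own figure.** The usual unpooled formula is n = [p₁(1−p₁) + p₂(1−p₂)] × (z₁₋α + z₁₋β)² / margin².
- Variance sum: 2 × 0.15 × 0.85 = 0.255.
- (1.645 + 0.842)² = 6.183.
- n = 0.255 × 6.183 / 0.0225 = 70.07, so 71 per arm.

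The stated 67 is not reproduced exactly. Power at 67 is Φ(0.15/√(0.255/67) − 1.645) = Φ(2.431 − 1.645) = 78.4%, close to the stated 80%. Other readings fit less well: one-sided 0.025 gives 89, the Farrington-Manning method 75, and a two-sided test of equality for 15% against 30% gives 121. The number is recognisably from a non-inferiority formula at one-sided 0.05. The gap between 67 and 71 is a separate matter.

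**2. How the two rules behave at 67 per arm.** I enumerated all pairs of binomial outcomes. The chi-square test is uncorrected and two-sided at 0.05. The margin rule requires the upper limit of the two-sided 90% Wald interval for LE minus TME to be below 0.15.

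| True LE / TME | Chi-square non-significant | Fisher non-significant | Margin rule met |
|---|---|---|---|
| 15% / 15% | 95.2% | 97.1% | 78.6% |
| 25% / 15% | 69.7% | 76.2% | 18.5% |
| 30% / 15% | 44.6% | 52.2% | 5.2% |

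- The last row lies exactly on the margin, where the margin rule should succeed about 5% of the time. It does, and a Newcombe interval gives 5.4%.
- In the first row, the design assumption, chi-square is significant in 4.8% of trials, and in LE's favour in 2.4%. The planned power is therefore not a property of that test. In 19.0% of trials chi-square is non-significant although the margin rule is not met.

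**3. One possible data set.** LE 18/67 (26.9%), TME 10/67 (14.9%).
- Difference: 8/67 = 11.9 points.
- Chi-square: pooled rate 28/134 = 0.209, standard error 0.0702, z = 1.70, p = 0.089, not significant.
- Interval: unpooled standard error 0.0695; upper 90% limit 0.119 + 1.645 × 0.0695 = 0.234, or 23.4 points.

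The equality test finds no difference, while the data remain compatible with an excess well beyond 15 points.

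**4. Effect of the interval level.** With a two-sided 95% interval (one-sided 0.025), power at 67 per arm is Φ(2.431 − 1.960) = 68.1% (67.8% by enumeration). The error at the margin is 2.6%, and 80% power would need 89 per arm.

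**The case against.** The best defence is that this is a condensed article. Its sentence on tests is generic: it covers every proportion, including baseline variables and the stoma rate, and does not single out the primary endpoint. Randomization and data management mentions a statistician who provided a data analysis plan, so a fuller document may hold the margin comparison. That much stands: nobody can say from this article that non-inferiority will never be tested.

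It does not remove the point, because Data analysis is not silent. It names the analysis set for the primary endpoint, the tests for proportions and the threshold, and those tests do not match the hypothesis. If an unshown plan contains the right test, the article's section still conflicts with it.

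The second defence is that the 45% and 52% rates assume a rule the article does not state. This also stands. A reader might infer from the Abstract that a non-significant p-value will be declared proof of comparability, but that sentence expresses a belief, not a decision rule.

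Two further readings should not be pressed. These are two-sided tests of equality, so calling the plan a superiority trial goes too far. And a significant excess with LE whose upper limit is still inside the margin is possible in principle but has probability of about 0.000002 at the design rates, so it carries no weight.

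**Conclusion.** The point holds in this form: the article states a non-inferiority hypothesis with a margin, then assigns proportions to tests that cannot address it. As written, those tests cannot establish non-inferiority, and the power claim belongs to an analysis that the section does not specify.

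The consequence is conditional. Only if non-significance were taken as comparability would the error at the margin be about 45% (chi-square) or 52% (Fisher) instead of about 5%. These figures assume 67 evaluable patients per arm, an absolute margin and a true TME rate of 15%. The mismatch itself needs none of those assumptions.

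It should be corrected before analysis, since it governs the primary conclusion. The margin and a level are already prespecified, so the design can be kept.

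**What to change.** In Data analysis, add a sentence for the primary endpoint, for example: *The risk difference (LE minus TME) in Clavien-Dindo grade 2 or higher complications within 30 days will be estimated with a two-sided 90% confidence interval; non-inferiority is concluded only if the upper limit is below 15 percentage points.* Name the interval method, such as Miettinen-Nurminen or Newcombe. State that a non-significant chi-square or Fisher test will not be read as non-inferiority, and keep those tests for other proportions. A follow-on superiority test is optional.

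In Sample size calculation, remove the conflict between two-sided and one-sided. The 90% interval follows the one-sided 0.05 given there. If the sponsor prefers a 95% interval, the article should acknowledge that power at 67 per arm falls to about 68%.

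With the 90% interval the cost is analysis wording only: no change to patients, procedures, data collection or sample size. Any fuller analysis plan should be checked for the same rule.

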### Secondary outcomes measures

Secondary outcomes will be as follows:Oncologic outcomes: 3-year disease-free survival (% DFS), 3-year overall survival (% OS), and recurrence rate (%).Functional outcomes: quality of life, as measured using EORTC QLQ-C30 (version 3) and rectal function, as measured using manometry, low anterior resection syndrome (LARS) score, and the Wexner Fecal Incontinence Score.The rate of permanent stoma formation (%).Factors affecting complete remission and the accuracy of mrTRG.Oncologic outcome in patient subgroups.

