#### Postoperative follow-up schedule

Patients will be followed for 3-year after surgery. Follow-up will consist of a physical examination and blood tests, including carcinoembryonic antigen (CEA) levels every 6 months after surgery. Chest X-ray and abdomino-pelvic CT every 6 months after surgery, chest CT will be performed every 6–12 months, and colonoscopy performed at 6–12 months and 24–36 months after surgery (Table 1).

**Table 1 Tab1:** Follow-up schedule and study procedure for study cohort

Documentation	Restaging	LE vs. TME	Visit 1	Visit 2–6
Study procedures	Screening	Surgery	Checking complications	Routine checkup
Period after pre-CRT	4–8 weeks	4–8 weeks	8–16 weeks	Every 6 months after Op.
Getting permission	●			
Screening	●			
Assigning serial number	●			
Demographics	●			
Physical exam	●		●	●
Heart/ lung evaluation	●			
Chest CT	●			● (Selective)
APCT	●			●
MR, rectal cancer	●			● (Selective)
Endoscopy	●			● (Selective)
Laboratory test	●		●	●
Endorectal sonography	●			
Manometry/questionnaire	●			● (Selective)
Checking complications			●	●
Selection of surgery type		●		

*Pre-CRT* Preoperative chemoradiotherapy, *Op*., Operation, *LE* Local excision, *TME* Total mesorectal excision, *CT* Computed tomography, *APCT* Abdomino-pelvic CT, *MR* Magnetic resonance

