#### Secondary study endpoints

1. Disease-free survival rate (%), overall survival rate (%) and recurrence rate (%) at 3 years.

2. Functional outcomes, including quality of life (EORTC-E030) and score of fecal incontinence (Wexner’s score) at 6, 12 and 24 months after surgery.

3. Rate of permanent stoma formation (%) at 3 years.

4. Accuracy of mrTRG (positive predictive value and negative predictive value).

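### Functional scores are scheduled at 6, 12 and 24 months, but the only tests named for continuous data are two-sample tests; used at each visit, these are open to modest bias from unequal missing scores (minor, secondary endpoints)

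*Protocol article*

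**What the plan says.** - **Timing.** Secondary study endpoints, item 2, sets quality of life and the "score of fecal incontinence (Wexner’s score) at 6, 12 and 24 months after surgery".
- **Instruments.** Secondary outcomes measures lists "quality of life, as measured using EORTC QLQ-C30 (version 3) and rectal function, as measured using manometry", with the LARS score and the Wexner score. It gives no visit times.
- **Schedule.** Table 1 (Postoperative follow-up schedule) has a row "Manometry/questionnaire". It is ticked at restaging, before surgery, and ticked as selective at visits 2–6.
- **Method.** Data analysis states: "Continuous data will be analyzed using Student’s t-test or Mann-Whitney U tests, as appropriate". The only regression for group outcomes is logistic: "Multivariate analyses using binary logistic regression will be used to assess the risk of postoperative complications".
- **Analysis set.** "The modified ITT set will be used for analysis of primary and secondary study endpoints".

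The article does not say whether the two-sample tests are run at each visit, on change from restaging or on a per-patient summary. It also does not say what happens to a patient with a missing score.

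**The concern.** A two-sample test takes one value per patient, and these endpoints have three post-operative values plus one at restaging. Run at 6, 12 and 24 months in turn, the tests answer three questions on three possibly different subsets of the modified ITT set. A patient with scores at 6 and 12 months contributes nothing to the 24-month result.

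Incomplete visits are foreseeable from the article itself. The follow-up questionnaire is marked selective, and completion could differ by arm because the operations lead to different aftercare and stoma rates.

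The Discussion argues that LE largely spares anorectal function and quality of life while TME does not. The trial's size was set for 30-day complications, so the functional comparison gets whatever precision is left. A distorted or imprecise 24-month comparison would weaken a main reason for offering LE.

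**Working it through.** **Inputs from the article.** 67 per arm and 5% dropout (Sample size calculation); three post-operative visits (Secondary study endpoints); a restaging questionnaire (Table 1); randomisation stratified by mrTRG 1 or 2 (Randomization and data management).

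**Assumptions, since the article gives none for these scores.** SD of 1 at each visit; equal correlation ρ between visits; two-sided 0.05. The article states no figure for the functional endpoints, so there is none to reproduce. The 67 per arm is taken as given.

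**Step 1: complete data.** At one visit the difference in means is unbiased, with SE = √(2/67) = 0.173 SD. The difference detectable with 80% power is (1.960 + 0.842) × 0.173 = 0.484 SD. Without a baseline term, a repeated-measures model with arm, visit, arm-by-visit and unstructured covariance returns the same difference at each visit. With complete data the t-test is therefore valid, and the model as such adds nothing at a given visit.

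**Step 2: where precision could come from.**
- *Restaging score.* Adjustment multiplies the variance by 1 − ρ². The detectable difference becomes 0.484 × √0.91 = 0.462 SD at ρ = 0.3, 0.484 × √0.75 = 0.419 at 0.5, and 0.484 × √0.51 = 0.346 at 0.7.
- *Averaging three visits.* The variance is multiplied by (1 + 2ρ)/3, which is 0.667 at ρ = 0.5 and 0.800 at 0.7. For a constant 0.4 SD difference, power goes from 63.9% at one visit to 80.9% and 73.5%. A t-test on each patient's mean has this same variance, so the gain belongs to averaging and not to the model.

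**Step 3: incomplete data.** Simulation: 67 per arm, true difference 0.4 SD at every visit, missing scores at 24 months only, log-odds of missingness changing by 1 per SD of the 12-month score.

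| Missing at 24 months, TME vs LE | Bias of the 24-month two-sample difference, ρ = 0.5 to 0.7 |
|---|---|
| equal (5% or 10% in both) | about 0 |
| 7.5% vs 2.5% | about 0.02 to 0.03 SD |
| 20% vs 10% | about 0.04 to 0.06 SD |
| 30% vs 10% | about 0.08 to 0.11 SD |

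In the unequal scenarios the bias is towards no difference. In the 20% and 30% rows, a likelihood-type estimate using the earlier scores was biased by less than 0.01 SD.

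Equal rates do not protect by themselves. In a second simulation (true difference 0.5 SD) the dependence on the earlier score was present in one arm only. With roughly 20% missing, the bias was about 0.08 SD (ρ = 0.5) and 0.10 SD (ρ = 0.7). With about 5% missing it was 0.02 SD.

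**Step 4: scale.** At low attrition, 0.03/0.17 ≈ 0.18 of a standard error. In the worst row, 0.11/0.19 ≈ 0.58 of a standard error, or 0.11/0.4 ≈ 28% of the assumed difference.

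**Step 5: stomas.** The Discussion reports a permanent stoma in about 30% of TME patients in the institution's own series. If that rate applied here, 0.30 × 67 ≈ 20 TME patients would have one. That the Wexner score does not apply to them is an inference; the article does not address it.

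**The case against.** **The sentence is generic, and the analysis plan is not shown.** The Data analysis sentence covers all continuous data, and handling of visits and missing scores is commonly left to the plan. This stands in part: the lack of a missing-data rule is no finding, and visit-by-visit testing is inferred. What remains is that the article does name a method for continuous data, and a better one exists for repeated scores.

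**A two-sample test need not be visit-wise.** A t-test on change from restaging or on each patient's mean fits the wording and uses within-patient information. Even at 30% versus 10% missing, comparing patients' mean available scores is biased by less than 0.01 SD when the effect is constant over time. This stands for the average effect. It does not give the results at 6, 12 and 24 months that the endpoint section asks for, and it is less safe if the effect changes over time.

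**The heavy attrition is assumed.** The article's only dropout figure is 5%, set alongside a 30-day endpoint. At that level the bias is small. This stands, which is why the range is shown.

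**Selective may mean selected visits.** Table 1 groups visits 2–6, and the mark may mean only that some of them include the questionnaire. The article does not settle this, so incomplete collection is foreseeable but not established.

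**Readings that go too far.** A reader might infer that all visits will be pooled in one t-test, with a type I error of about 17–21%; nothing in the article suggests pooling. A reader might also credit a mixed model with raising power from 64% to 74–81%; Step 2 shows that this comes from averaging. Nor are the named tests invalid: in a randomised trial a visit-wise test is sound when scores are complete.

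**Conclusion.** The point holds as a minor one, for secondary endpoints only. The primary endpoint and the sample size are untouched. For the functional scores, the named tests in their natural visit-wise use ignore the restaging score and the patient's other visits, and rest on whoever is observed at that visit. Bias arises only if missingness depends on earlier scores and does so, or occurs, unequally between arms. It is about 0.02–0.03 SD at 7.5% versus 2.5% missing and up to about 0.11 SD at 30% versus 10%. These figures rest on an assumed correlation of 0.5–0.7, an assumed missingness mechanism and 67 per arm. The article does not show that patients will be dropped, or that attrition will be heavy.

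**What to change.** 1. In Data analysis, name one mixed model for repeated measures for each functional score measured repeatedly. Include arm, visit, arm-by-visit, the restaging score and the mrTRG stratum, with unstructured within-patient covariance, and every patient with at least one post-operative score.
2. Report the arm difference with its 95% CI at each visit and averaged over visits. A bootstrap interval is a reasonable check where scores are skewed. Keep the t-test and Mann-Whitney test for variables measured once.
3. Reconcile the selective mark in Table 1 with the fixed times in Secondary study endpoints, stating whether it refers to visits or to patients.
4. Report separately, by arm, patients whose stoma makes the Wexner score inapplicable. Do not let the model treat those scores as missing at random.

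**Cost.** A few sentences and slightly more programming, with no new visits or data. The article says "all analyses will be performed using SPSS software, version 22", and that package fits mixed models. Two downsides remain: the model assumes missingness depends on observed scores, and the average can hide a time trend, which is why the visit-specific differences are kept.

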### Safety

The main outcome will be the detection and documentation of postoperative complications. The severity of complications will be classified according to the Clavien-Dindo Classification Grade and will be registered in the case reporting form. Currently, the oncologic outcome of pre-CRT followed by LE is considered to be equivalent to that of pre-CRT followed by TME for patients who respond well to pre-CRT. If the pathologic results show ypT2 with risks, ypT3 or ypT4, surgeons will recommend to perform TME for oncologic safety of the participants. The current study will meet with all local legal requirements and meet all requirements of the ICH Guideline for Clinical Safety Data Management, Definition and Standards for Expedited Reporting, Topic E2A.

## Discussion

Although pre-CRT followed by TME has become the standard treatment for patients with locally advanced rectal cancer, recent evidences suggests that organ-preserving strategies such as LE and watchful waiting can be used as an alternatively to TME in patients with a favorable response to pre-CRT without compromising oncologic outcomes and high rate of major LARS [14–19, 31]. Numerous tools can be used to assess the tumor response after pre-CRT, including physical examination, endorectal ultrasound, endoscopy, and MRI. MR staging is currently considered one of the most useful methods of evaluating the response to pre-CRT [20, 24, 25]. However, the accuracy rate of mrTRG for predicting pCR is only approaximately 60% [25]. Considering that ypT status reflects the ypStage and that patients with pCR or ypT1N0M0 have a more favorable prognosis [29], accurate examination of tumor status is needed.

Recently, our institution reported a retrospective analysis demonstrating that oncologic outcomes of pre-CRT followed by LE were comparable to those of TME, even in patients with lymph node involvement [27]. A recent meta-analysis also suggested that there are no differences in local recurrence rates, disease-free survival, and overall survival between rectal cancer patients that received LE or TME [28]. In patients with early-stage rectal cancer, several studies found that LE did not compromise the oncologic outcome but did result in organ preservation [28]. Based on previous studies, if lymph nodes are positive after pre-CRT, patients are optimally treated with TME with regional lymph node clearance, in line with the current standard of treatment [29], but a patient that achieves a complete or near-complete response after pre-CRT can consider LE.

In terms of postoperative complications, only one patient (2.1%) in our previous study developed a postoperative complication (perianal fistula) that required prolonged hospitalization [27]. In a recent prospective study of LE in patients with T2 rectal cancer, surgery-related adverse events above grade 3 occurred in 16 patients (21%) and grade 1 or 2 complications occurred in 50 patients (65%) [26]. Although complications of LE after pre-CRT are generally less severe than complications of TME, the rate of overall complications including dehiscence of the rectal suture line resulted from anal pain are higher than TME after pre-CRT [26]. Based on the assumption that the oncologic outcomes of LE and TME are similar for patients with a favorable response (mrTRG 1 or 2) after pre-CRT, further prospective studies on surgical outcomes in LE after pre-CRT are needed.

Pre-CRT followed by LE causes minimal loss of anorectal function and quality of life, similar to watchful waiting [26]. TME results in postoperative loss of anorectal, urinary and sexual function, and also carries the risk of permanent stoma formation [10]. In mid-to-low advanced rectal cancer, the use of pre-CRT has decreased the rate of permanent stoma formation; however, in our recent study, approximately 30% of patients receiving TME after pre-CRT did develop a permanent stoma [27]. A recent prospective study suggested that pre-CRT followed by LE might be an alternative to TME for patients with rectal cancer who have a favorable response to pre-CRT or who seek organ preservation because the Fecal Incontinence Severity Index (FISI) score and the Functional Assessment of Cancer Therapy-Colorectal (FACT-C) scores did not substantially decrease after surgery [26].

Previous studies, even prospective studies for LE or watchful waiting, suffer from the lack of standardized selection criteria. Recently, the MECURY group convened multidisciplinary teams (MDT) to decide which patients should defer surgery and which patients should receive standard treatemtn after pre-CRT [22]. Our institution also reported that case discussions in MDT meetings resulted in altered clinical decisions in > 10% cases for advanced and recurrent colorectal cancer [32]. Based on this experience, in the current study, specialized faculty, including a colorectal surgeon, radiologist, medical oncologist, radiation oncologist, gastroenterologist, and pathologist, will select the study patients that show a favorable response after pre-CRT. The data on postoperative complications in LE and TME after pre-CRT collected through the current study will provide valuable information about the risk factors of LE after pre-CRT.

This prospective study has some weaknesses because this study will be performed based on the real practice in our institution. Recent studies insists that the interval between completion of pre-CRT and the assessment of tumor response is increased up to 12 weeks and this longer interval might increase the rate of pathologic CR [33, 34]. On the other hand, in this prospective study, TME is undertaken 6–8 weeks after the completion of pre-CRT according to the real practice in our institution. The schedule of restaging is designed within 2 weeks before surgery considering waiting time of MRI in our institution and minimizing dropouts, however, almost patients have restaged at 2 or 3 days before surgery on the real practice. About 10% of lymph node infiltration and the 15% of local recurrence in the ypT2 were worrisome for this study [27, 29, 35]. Nevertheless, recent reports showed the overall survival was not significantly different between the LE and TME groups [27, 36, 37]. The evidences of LE for ypT2 tumors are still lack, therefore, our study determines the effect of LE in ypT2 tumors on oncologic outcomes.

